# An evaluation of an intervention designed to help inactive adults become more active with a peer mentoring component: a protocol for a cluster randomised feasibility trial of the Move for Life programme

**DOI:** 10.1186/s40814-019-0473-y

**Published:** 2019-07-09

**Keywords:** Physical activity, Exercise, Peer mentor, Inactive adults, Train the trainer, Cascade model, Sedentary, Scalability

## Abstract

**Background:**

There is overwhelming evidence to support the promotion of physical activity in adults in terms of benefits to well-being, physical and mental health. Physical activity guidelines suggest that adults should accumulate at least 150 min of moderate to vigorous physical activity per week. In Ireland, the majority of adults do not achieve these guidelines, with costs to health and economy. ‘Move for Life’ (MFL) employs behavioural change techniques delivered by an instructor and peer mentor, using a train-the-trainer (cascade) model. This study will conduct a feasibility cluster randomised controlled trial of the MFL intervention for modifying physical activity behaviours in inactive adults aged 45 years and older.

**Methods:**

The trial is set in eight Local Sports Partnership (LSP) hubs that have structured physical activity programmes. The hubs are the units of randomisation (clusters), and individuals are the units of analysis (participants). Eligible participants will contact one of the hubs, with each hub running four physical activity programmes. Each programme requires between 12–15 inactive adults, resulting in 48–60 participants per hub. Allowing for 20% dropout rate, an additional 96 people will be recruited giving a maximum sample of 576. The hub will be randomised: true control, usual programme or MFL intervention. The true control group will be given information about physical activity but will not be included in a programme for the duration of the trial; the intervention will involve the instructor training one (or more) of the participants to be a peer mentor using an educational toolkit; and usual care groups will have physical activity classes delivered as normal. Baseline data will collect physical activity measures and follow-up measurements will be obtained at 3 and 6 months. All participants will be asked to wear a device for measuring activity on the thigh (activPAL) for 7 days before commencing the programme and at 3 and 6 months. The primary objective of the study is to investigate if it is feasible to deliver the intervention and collect data on moderate to vigorous physical activity (MVPA) on all participants, thereby providing valuable information to guide sample size calculation for a future, more definitive trial.

**Trial registration number:**

ISRCTN11235176

**Electronic supplementary material:**

The online version of this article (10.1186/s40814-019-0473-y) contains supplementary material, which is available to authorized users.

## Background

Being physically active has significant benefits for health and well-being with evidence to show that meeting physical activity guidelines (PAGL) promotes physical and mental health [1–3]. There is evidence that attaining moderate to vigorous physical activity (MVPA) levels that may even be below the recommended 150 min per week can significantly reduce mortality rates, and when the time spent in MVPA is increased, the protective benefits increase accordingly [4]. Age is a significant negative determinant of physical activity, which declines by two-thirds between the ages of 20 and 90 [5]. Despite this gradual decline, those who do engage in physical activity as they age have increased odds of maintaining well-being in later life [6]. Being inactive is associated with a range of poor health outcomes and increased all-cause mortality [7]. Furthermore, physical inactivity in older adults reduces mobility and functional independence [8], with negative consequences for social participation and emotional health. Internationally, the social and economic costs of physical inactivity are recognised but national policies in many countries, including Ireland, to increase physical activity levels remain weak [9]. There is strong evidence to show that complex interventions based on behavioural change strategies can both increase [10] and maintain [11] physical activity levels. Interventions such as these have been shown to reduce the incidence of falls in older adults [12]. Likewise, available evidence shows that interventions aiming to increase social support for participation by fostering positive group dynamics can increase physical activity [13]. Peer-delivered interventions could have considerable, positive public health implications in terms of expanding the reach of such efforts [14].

Move for Life (MFL) has been developed to broaden the reach of the professional which, in this research programme, involves the Local Sports Partnership (LSP) instructor to the participants via peer mentor support. LSPs are geographically structured and state-funded community-based organisations whose specific purpose is to provide approved and structured exercise classes for the communities they serve, using professional instructors. Move for Life will train the professional instructors to facilitate behaviour change by teaching individual behaviour change skills, implementing social support strategies and creating favourable group dynamics. Peer mentors will be trained in ways to keep the group together for the purpose of continuing their physical activity after the standard LSP programme finishes (Fig. 1). If effective, it will maximise the impact of PA (physical activity) programmes, run by Local Sports Partnerships (LSPs), increasing the likelihood of real change, sustainability and scalability. Cascading models (also commonly called train-the-trainer models) have the potential to be time and cost-effective and are widely used in medicine [15] and prevention [16, 17]; however, this method requires rigorous examination [18] in community-based physical activity interventions.

**Fig. 1 Fig1:**
[figure not shown]
The Move for Life peer mentor model cascading professional impact

Move for Life aims to augment and complement existing physical activity programmes in counties Clare (with a population of 117,000) and Limerick (with a population of almost 200,000) in the Mid-West region of Ireland initially. The University of Limerick, where most of the academic team is based, has research links with the Local Sports Partnerships of counties Limerick and Clare. These counties cover one whole Health Service Executive Community Health Organisations (HSE CHO) area. These counties, both with distinctive urban dwelling and rural populations, were selected both for convenience to the academic location and for their potential to replicate the national demographic.

A well-designed, rigorously conducted randomised controlled cluster trial (RCT) is required to provide evidence of potential for a comprehensive MFL intervention. Prior to such a definitive trial, a feasibility study is required. MFL will provide this using a feasibility cluster RCT design; it will advise the selection of RCT primary and secondary outcomes and develop our understanding of the impact on hard to reach inactive adults from the professional-peer-participant cascading model of intervention. The purpose of MFL is to increase the daily time spent in MVPA among inactive people aged 45 and over.

The study hypothesis is that it is feasible to deliver the MFL intervention and to measure the time spent in daily MVPA by participants. Therefore, the primary aim is to investigate the feasibility of the trial and data collection. Specific objectives are to record numbers recruited, retention and attrition rates, safety and acceptability of the intervention and measurements and follow-up testing attendances and participant compliance. The secondary aim is to obtain preliminary information on the economic impact of the trial on participants. Accordingly, secondary objectives are to collect data on health costs and quality of life for participants in each arm of the study for the duration of the trial (Fig. 1).

## Methods

The trial will be reported according to the CONSORT extension for randomised pilot and feasibility trials [19] (see Additional file 1 for the CONSORT checklist). The following phases will be run sequentially: screening, enrolment, allocation, follow-up and assessment.

### Study design

Move for Life is a feasibility cluster randomised control trial (RCT) where the LSP hubs are the units of randomisation (the clusters), and individuals within the hubs are the units of analysis (the participants). The advantage of a cluster RCT is that it overcomes contamination problems that arise if a simple random allocation is used. When testing a complex intervention, randomisation of participants risks contamination if individuals from both arms attend the one group. This study will enrol a total of eight hubs and randomise physical activity groups to each of three arms. This framework is in line with the recommendations of Eldridge et al. [20] and the CONSORT [19] guidance on the minimum number of clusters required to obtain accurate estimates of rates and proportions in pilot and definitive cluster RCTs, respectively. The first arm is the Move for Life intervention (three hubs), the second is the usual programme (three hubs) and the third is the true control (two hubs).

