### Sample size justification

As this is a feasibility study, a formal sample size calculation has not been used but the sample size was estimated based on the primary outcome of interest, which is the feasibility of measuring MVPA. The minimum numbers required to sustain structured physical activity programmes and necessary group dynamics. Each programme involves an instructor working with a group and, for feasible group dynamics, requires between 12–15 inactive adults. If each hub involves four physical activity programmes, it will give a sample of 48–60 participants per hub—a total of 480 participants. Allowing for a 20% dropout rate, an additional 96 people will be recruited giving a maximum sample of 576.

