### Randomisation process

The hubs will be the unit of randomisation and will be randomised to each arm. Each hub (cluster) will be geographically separated to reduce contamination effect. Clusters will be stratified as rural or urban. Hubs will be randomised to one of the following: true control (two hubs), usual programme (three hubs) or MFL intervention (three hubs). Participants in the true control group will be given information about physical activity but will be placed on a waiting list for access to the MFL physical activity programmes for the duration of the trial. They will be offered the programmes after the trial. The participants allocated to the MFL intervention group and the usual physical activity programmes will not be aware of their status. Randomisation will only occur and will only be revealed to participants and their instructors after all the baseline data have been collected.

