## Outcomes

The primary outcome of the study is to investigate the feasibility of measuring MVPA. The acceptability and safety of the intervention and measurement methods will be investigated. The data will provide reliable estimates for sample size calculation for a future definitive trial. Secondary outcomes relate to data on recruitment, allocation, retention, attrition and attendance. Data will be collected on safety and adverse events will be recorded by the LSP tutor. Participant recruitment outcomes include demographic profile and the success of each of the recruitment strategies. Participant retention outcomes include the number, profile and reasons of participants that drop out. Data will be collected on the numbers who complete each part of the physical activity measures and questionnaires and who wear and return the activPAL devices. Questionnaires will enable the collection of data on healthcare resource use, out-of-pocket expenses and health-related quality of life. For each secondary outcome, the point estimate of effect will be reported, and precision will be presented with 95% confidence intervals. SPSS version 25 will be used for the statistical analyses. At specific time-points, immediately post intervention and 3 months post intervention, follow-up testing sessions will take place. The authors define ‘minimum thresholds’ in the context of the post intervention and 3-month follow up testing as the minimum proportion of participants that attend the testing sessions and provide reliable data.

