### Analysis plan

As this is a feasibility study, the analysis will focus on confidence interval estimation. Accordingly, any hypothesis testing or regression modelling will be considered entirely exploratory in nature. Demographics and baseline characteristics of all randomized participants will be summarized for each group as well as overall. Continuous variables will be reported as mean ± standard deviation. Categorical variables will be reported as *n* and percentage. The research team analysing the data will be blinded as to the affiliation of each hub. An exploratory analysis of cost-effectiveness, in terms of estimated cost and quality-adjusted life years (QALYs), will be presented.

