## Abbreviations

BCW: Behaviour change wheel
BMI: Body mass index
ICC: Intra-cluster coefficient
LSP: Local Sports Partnership
LSPs: Local Sports Partnerships
MFL: Move for Life
MVPA: Moderate to vigorous physical activity
MVPA: Moderate to vigorous physical activity
PA: Physical activity
PAGL: Promotes physical and mental health
RCT: Randomised controlled cluster trial
RCT: Randomised controlled trial

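### Hubs are randomised and confidence intervals are the focus of the analysis, but nothing stated ties those intervals to the hubs, so analysing individuals as independent would make them too narrow

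*Protocol article*

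**What the plan says.** Under Randomisation process the protocol article states: "The hubs will be the unit of randomisation and will be randomised to each arm". The split is "true control (two hubs), usual programme (three hubs) or MFL intervention (three hubs". Study design (and the Abstract) then name the other unit: "individuals within the hubs are the units of analysis (the participants".

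Two sections describe the inferential output. Under Analysis plan, "the analysis will focus on confidence interval estimation", and any testing or regression model is given exploratory status only. Under Outcomes, "For each secondary outcome, the point estimate of effect will be reported, and precision will be presented with 95% confidence intervals". The secondary outcomes listed there include recruitment, retention, attrition and attendance. The same section promises estimates good enough to size a later definitive trial, which the Background describes as a cluster trial.

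Sample size justification counts heads: "it will give a sample of 48–60 participants per hub—a total of 480 participants", then "Allowing for a 20% dropout rate, an additional 96 people will be recruited giving a maximum sample of 576". No design effect is mentioned. The only trace of within-hub correlation is the entry "ICC: Intra-cluster coefficient" under Abbreviations. The term is not used in the text, given a value or named as a result to be reported.

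**The concern.** In a cluster trial the information about an arm difference comes mainly from the number of hubs and how much they differ, not from the head count. A 3 v 3 comparison has 4 degrees of freedom between hubs, however many people attend. An interval that treats about 60 people in one hub as independent ignores this and shows precision that the design cannot deliver.

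There are reasons in the article to expect hubs to differ. Participants share instructors, the intervention sets out to build group cohesion and peer support, and Limerick and Clare start in different seasons, which the Discussion expects may affect activity outcomes.

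Two things are at stake. First, with testing set aside as exploratory, the intervals are what readers will use to judge precision. The usual individual-level tools for clustering, a mixed model or GEE, are regression models and so fall in the exploratory tier, while the headline intervals sit outside it. Second, the sample size of a definitive cluster trial needs an ICC, and none is a planned output.

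**Working it through.** **The plan's own figures.** 8 hubs × 4 programmes × 15 people = 480 (with 12 per programme, 384). 480 × 1.20 = 576. Both stated figures reproduce, and neither contains a design effect.

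**Inputs.** Hubs per arm: 3, 3 and 2 (Randomisation process). People per hub: 576 / 8 = 72 recruited, and 72 × 0.80 = 57.6, so m = 58 analysed. The ICC is not in the article; 0.01 to 0.10 is my assumption. Hub sizes are taken as equal.

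**Formulas.**
- Design effect: DE = 1 + (m − 1) × ICC.
- Actual coverage of an unadjusted 95% interval: 2Φ(1.96/√DE) − 1.
- Width of a hub-based interval relative to the unadjusted one: √DE × t / 1.96. Here t = 2.776 for 3 v 3 hubs (4 df) and 3.182 for 3 v 2 hubs (3 df). If the between-hub variance is pooled over all three arms, t = 2.571 (8 − 3 = 5 df).

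For example, at ICC 0.05: DE = 1 + 57 × 0.05 = 3.85 and √DE = 1.96. Coverage is 2Φ(1.00) − 1 = 68%. The 3 v 3 ratio is 1.96 × 2.776 / 1.96 = 2.8.

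| ICC (assumed) | DE | √DE | Coverage of unadjusted 95% interval | Ratio, 3 v 3 (4 df) | Ratio, 3 v 2 (3 df) | Ratio, pooled (5 df) |
|---|---|---|---|---|---|---|
| 0.01 | 1.57 | 1.25 | 88% | 1.8 | 2.0 | 1.6 |
| 0.03 | 2.71 | 1.65 | 77% | 2.3 | 2.7 | 2.2 |
| 0.05 | 3.85 | 1.96 | 68% | 2.8 | 3.2 | 2.6 |
| 0.10 | 6.70 | 2.59 | 55% | 3.7 | 4.2 | 3.4 |

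The √DE column is the part due to correlation alone. The ratio columns add the cost of having few hubs.

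**A very small ICC.** At ICC 0.005 and m = 60, DE = 1 + 59 × 0.005 = 1.295 and √DE = 1.14. Even so, the ratio is 1.14 × 2.776 / 1.96 = 1.6 for 3 v 3 and 1.14 × 3.182 / 1.96 = 1.85 for 3 v 2.

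**A proportion.** Take 60% completion over all 576 people (m = 72). Unadjusted: 1.96 × √(0.24/576) = 4.0 percentage points. At ICC 0.05, DE = 1 + 71 × 0.05 = 4.55 and the standard error is √(0.24/576 × 4.55) = 4.35 points. The half-width is then 2.365 × 4.35 = 10.3 points if the eight hubs are treated as one sample (7 df), or 2.571 × 4.35 = 11.2 points if arm is respected (5 df).

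**The case against.** The strongest answer is that the quoted sentence does not describe an error. Calling individuals the units of analysis is ordinary cluster-trial wording, and it fits a mixed model, GEE or cluster-robust interval, all of which analyse individuals. Nowhere does the article say that clustering will be ignored. It cites cluster-trial guidance for the number of hubs, stratifies the hubs and lists the ICC as an abbreviation. It is also a condensed article whose analysis plan is not shown, and interval methods are commonly left to such a plan.

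Much of this stands, and it rules out three stronger readings that a reader might infer:

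- That the article commits the trial to an unadjusted analysis. It does not; it is silent on adjustment.
- That the intervals are certain to be far too narrow. This needs both an unadjusted analysis and an ICC that the article does not give. At ICC 0.005 to 0.01 with m = 60, correlation alone changes the width by 14% to 26%; the larger ratios also count the few degrees of freedom.
- That progression depends on these intervals. The 95% intervals are tied to secondary outcomes, and the Progression criteria are fixed cut-offs (40%, 40%, 80%) that mention no interval.

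The objection does not clear the point. The article has its own Analysis plan section, and that section makes intervals the focus and puts regression modelling in the exploratory tier. Together with the named unit, an analyst who follows the text literally arrives at individual-level intervals. The promise of planning estimates for a cluster trial, with no ICC among the outputs, is a gap in what the article itself sets out to deliver.

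**Conclusion.** The point holds in conditional form. As written, the article pairs randomised hubs with individuals as units of analysis and an interval-based analysis, and states nothing that links the intervals to hubs. If individuals are then treated as independent, a nominal 95% interval for an arm difference covers about 88% at ICC 0.01 and 55% at ICC 0.10, and a 3 v 3 hub interval on 4 df is about 1.8 to 3.7 times as wide.

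The direction is sure for any positive ICC. The size rests on the assumed ICC range, about 58 people per hub, equal hub sizes and the choice of degrees of freedom. The Discussion allows some hubs to run three programmes and others four; unequal sizes would tend to raise the design effect somewhat.

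**What to change.** Add to the Analysis plan that every confidence interval, for arm differences and for retention, completion and attendance proportions, accounts for hub clustering and the small number of hubs. Name one of two methods:

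- hub-level means or proportions, with t degrees of freedom based on the number of hubs; or
- an individual-level mixed model with a random hub effect and Satterthwaite degrees of freedom.

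Say that this model serves the main estimates and is not part of the exploratory modelling. Adjust MVPA for its baseline value, and for the urban/rural stratum as far as the few hubs allow: the stratum term uses one hub-level degree of freedom, which takes a 3 v 3 contrast from 4 to 3.

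List the hub ICC with its confidence interval, for MVPA and for completion, as a planned output for the definitive trial. With eight hubs that interval will be wide, and the report should say so. The phrase about units of analysis may stay once the adjustment is stated.

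The cost is wider reported intervals and a little more analysis work. Recruitment, allocation and data collection do not change.

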### Study overview

The trial is set in eight Local Sports Partnership (LSP) hubs that have ongoing structured physical activity programmes. LSPs are state-funded community-based organisations whose specific purpose is to provide approved and structured physical activity classes for the communities they serve, using professional instructors. Eligible participants will contact one of eight regional hubs, with each hub running four physical activity programmes. These include Men on the Move, Women on Wheels, Go for Life and Get Ireland Walking. Each hub will be randomised to one of the following: true control, usual programme or MFL intervention. The intervention will augment existing programmes by training professional instructors to implement individual and group-based behaviour change strategies, assisted by peer mentors that will help keep the group together after the lifetime of the programme. The true control group will be given information about physical activity but will not be included in a programme for the duration of the study; usual programme groups will have physical activity classes delivered as normal. Baseline data will be collected on physical activity measures and follow-up measurements will be obtained at 3 and 6 months. Participants in all groups will be asked to wear a lightweight device for measuring activity on the thigh (an activPAL) for 1 week before commencing the programme and again at 3 and 6 months. An Adverse Events Reporting System will be in place, reporting back to the Move for Life advisory committee, who will make decisions about trial safety and continuance. Ethical approval for the study was granted by the University of Limerick, Faculty of Education and Health Sciences Research Ethics Committee (reference number—EHS_2018_02_15, approved on April 9, 2018) (Fig. 2).

